#### Allocation Implementation

Participants will be randomly assigned to any group with a 1:1 allocation through a website. The web system will generate randomization based on the rand() function of the PHP language. Through this function, a random number between 0 and 3 is generated and subsequently assigned to the participants upon recruitment. Depending on the random number assigned, a QR code will be sent to the participants, which will allow them to download a version of the app that contains the strategies pertinent to their study group.

### Assignment of Interventions: Blinding

#### Who Will Be Blinded?

This is a double-blinded trial, blinded to the participants and the research team. A data analyst will work with the final data set, where the group condition will be masked.

#### Procedure of Unblinding If Needed

Unblinding will not occur in this study.

### Data Collection and Management

#### Plans for Assessment and Collection of Outcomes

Self-report questionnaires assessing primary and secondary outcomes will be administered at baseline (immediately before intervention), post intervention, and follow-up. Primary outcomes will be assessed through the website and the app, and secondary outcomes will be measured only on the website.

#### Plans to Promote Participant Retention and Complete Follow-Up

Participants will receive extensive information about the study setup and requirements during the recruitment. This information will include and stress the importance of completion of the follow-up.

#### Data Management

After the participants have completed the web-based questionnaires both on the website and on the app, we will enter the confidential data into a secure platform without identifying information, as each participant will be assigned an encrypted ID number. Only the lead investigator, the research assistants in charge of partial data entry, and the statistician will have access to the complete database. All people with access to the data set will need to sign a confidential agreement to assure the commitment to not reveal identifying information.

### Statistical Methods

#### Statistical Methods for Primary and Secondary Outcomes

We will use descriptive statistics to assess balance across groups at baseline. The primary between-group analysis will be carried out on an intention-to-treat basis for GAD-7 and PHQ-9 scores. We will use a linear mixed model for repeated measures (MMRM) analyses to compare all the intervention and control groups regarding the change in all outcome measures from baseline to post intervention and at follow-up. All the models will be adjusted for sex, age, educational level, and concurrent psychological or psychiatric treatment. Analysis will be carried out with SPSS 26 (IBM Corp) and Stata 15.01 (StataCorp).

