### Recruitment and Informed Consent

For recruitment, invitations will be made through the social networks of the Center for Applied Psychology and the Faculty of Psychology of the University of Talca. In addition, the educational and health services of 4 districts in the region will be contacted to disseminate the multiplatform application Cuidandome to adults. The call for participation will include an explanatory video and an informed consent form, which will be available on and collected through the project website (under development). Participants will be recruited through convenience sampling and will be randomly assigned to 1 of the 4 groups by means of simple randomization (through the PHP: Hypertext Preprocessor rand() function).

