### Outcomes

#### Primary Outcomes

Anxiety symptom is 1 of the 2 primary outcomes, and it will be measured by the Generalized Anxiety Disorder–7 Scale (GAD-7). It consists of 7 items that the person assesses on a scale of 0-3 according to the frequency with which each symptom has disturbed them during the past 2 weeks [23]. It shows high reliability in Chilean samples (Cronbach α=0.86 [24]).

Depression symptoms will be measured by the PHQ-9 depression scale, which consists of 9 items that evaluate the presence of depression symptoms present in the past 2 weeks, with a response scale of 0=never, 1=some days, 2=more than half the days, and 3=almost every day. With a Cronbach α of 0.83, its reliability is high in Chilean samples [25]. Additionally, depression and anxiety symptoms in the past week will be assessed through the Patient Health Questionnaire–4 (PHQ-4) [26].

Primary and secondary outcomes will be assessed at 3 time points: preintervention (baseline), immediately post intervention (30 days post intervention), and 1-month follow-up in all groups.

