### Sample Size

To achieve the aims of the study, we have considered 4 arms. To obtain a statistical power of 0.80, a minimum sample size of 36 participants is required for each of the 4 arms. Controlling for a dropout rate of 26%, as shown by the literature on behavioral experiments linked to mobile apps for symptoms related to mood and anxiety [32,33], a final sample size of 49 participants per group is required. The sample size approximation was made based on the literature on statistical power and sample sizes in clinical and social science research [34], while the estimate to reduce the effects of the percentage of abandonment in the experimental conditions was calculated based on Wang and Ji [33]. Thus, an estimate of 196 participants sufficiently obeys such parameters. In addition to the quantitative data collection, a qualitative collection of information will be carried out through focus groups. Regarding the number of focus groups, a total of 4 have been established, 1 for each study group. The size of the focus groups, following the recommendations in the literature [35], is estimated at a total of 32 participants (reaching an estimate of the saturation point), that is, 8 participants per focus group.

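### The covariate list fixed for all models leaves out the baseline score of the outcome, which costs precision unless the arms are given a common baseline mean

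*Protocol article*

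**What the plan says.** Under Statistical Methods for Primary and Secondary Outcomes, the article plans a mixed model for repeated measures to "compare all the intervention and control groups regarding the change in all outcome measures from baseline to post intervention and at follow-up". The primary outcomes are named there: "The primary between-group analysis will be carried out on an intention-to-treat basis for GAD-7 and PHQ-9 scores". The adjustment set follows: "All the models will be adjusted for sex, age, educational level, and concurrent psychological or psychiatric treatment".

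Under Primary Outcomes there are three assessments. The first two are "preintervention (baseline), immediately post intervention", and the third is the 1-month follow-up. A baseline value is therefore planned for every outcome.

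Baseline has two stated uses: a descriptive check of balance, and the reference point for change. It is not named as a covariate anywhere. The article does not say whether it enters the model as one of the repeated responses or, if so, whether the arms share one baseline mean.

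**The concern.** The earlier score on the same scale is usually the best single predictor of the later one. The plan lists covariates for every model and leaves that one out. An analysis plan written to follow the sentence literally would have no baseline term.

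Two things are at stake.

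- **Precision.** A comparison of change that does not condition on baseline carries more residual variance than one that does. With 36 evaluable participants per arm, this matters.
- **Chance imbalance.** If an arm happens to start higher, regression to the mean moves its change score for reasons unrelated to the app. The descriptive balance check would show this but not correct it.

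**Working it through.** **Inputs from the article.** Sample Size: "To obtain a statistical power of 0.80, a minimum sample size of 36 participants is required for each of the 4 arms", then 26% dropout, giving 49 per arm and 196 in total. Assessments: three. Allocation: equal across four arms, "by means of simple randomization".

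**Inputs not in the article, so assumed.** The baseline-to-outcome correlation r (0.4 to 0.7, with 0.3 and 0.8 also shown); equal variances at each visit; complete data; no credit for the four listed covariates. For power: a pairwise contrast at two-sided 0.05.

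**Step 1: the plan's own figure.** 36 / (1 - 0.26) = 48.6, rounded up to 49; 4 x 49 = 196. This reproduces. The 36 itself cannot be derived, because no effect size, SD, significance level or test is given.

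**Step 2: variance with and without baseline.** With the outcome variance set to 1:

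- change score without a baseline covariate: 2(1 - r)
- baseline-adjusted: 1 - r²
- ratio, adjusted to unadjusted: (1 - r²) / [2(1 - r)] = (1 + r)/2
- share of information lost without adjustment: 1 - (1 + r)/2 = (1 - r)/2

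| r (assumed) | change | adjusted | ratio | loss |
|---|---|---|---|---|
| 0.3 | 1.40 | 0.91 | 0.65 | 35% |
| 0.4 | 1.20 | 0.84 | 0.70 | 30% |
| 0.5 | 1.00 | 0.75 | 0.75 | 25% |
| 0.6 | 0.80 | 0.64 | 0.80 | 20% |
| 0.7 | 0.60 | 0.51 | 0.85 | 15% |
| 0.8 | 0.40 | 0.36 | 0.90 | 10% |

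**Step 3: does a repeated-measures model recover the loss by itself?** Generalized least squares was run for two arms of 36 and three visits, with compound symmetry and baseline as a response. The variance of the arm difference in change was:

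| r | free arm means at baseline | common baseline mean | ratio |
|---|---|---|---|
| 0.4 | 0.0667 | 0.0467 | 0.70 |
| 0.5 | 0.0556 | 0.0417 | 0.75 |
| 0.6 | 0.0444 | 0.0356 | 0.80 |
| 0.7 | 0.0333 | 0.0283 | 0.85 |

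With free arm means at baseline, the model matches the plain change score. With a common baseline mean, it matches baseline adjustment and nothing is lost. The model's name does not settle the matter; the handling of baseline does.

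**Step 4: power.** The article does not say which analysis the 36 per arm presumes, so both cases are shown.

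- If 36 gives 80% for the unadjusted change, baseline adjustment gives about 92%, 90%, 88% and 86% at r = 0.4, 0.5, 0.6 and 0.7. Equivalently, 80% would need 36(1 + r)/2 = 25.2, 27.0, 28.8 or 30.6 evaluable per arm.
- If 36 gives 80% for a baseline-adjusted analysis, the unadjusted change has about 65%, 68%, 71% and 73%.

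**Step 5: chance imbalance.** With 49 per arm, the standard error of a baseline difference between two arms is √(2/49) = 0.20 SD. A difference of 0.3 SD or more in either direction has probability about 0.14 for any one contrast. If it occurs, the unadjusted change contrast shifts by 0.3(1 - r): 0.18 SD at r = 0.4 and 0.09 SD at r = 0.7.

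**The case against.** The strongest reply is that the article does not commit to the inefficient model. It names four covariates without saying they are the only ones, and a condensed article commonly leaves the model equation to the full protocol or analysis plan. A repeated-measures model with baseline as a constrained response fits the wording, needs no baseline covariate and loses nothing.

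Part of this stands: the loss is conditional and could be zero. But the article is not silent on covariates. It sets them for every model and leaves out the one that bears most on a comparison of change. It does not state the common-mean constraint, and Step 3 shows that a repeated-measures model without it gains nothing over a change score.

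Several stronger readings are tempting and are not supported:

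- **The plan wastes 15% to 30% of its information, as a fact.** That range needs r between 0.7 and 0.4, which the article does not give, and one form of a model it leaves open. Dropout, unequal variances or useful covariates would change it.
- **Simple randomization makes baseline imbalance likely.** Its main effect is to let arm sizes vary. Unstratified blocking would not balance symptom scores either, and 0.3 SD or more is roughly a one-in-seven event per contrast.
- **Wide entry criteria make the loss larger.** If baseline scores do vary widely, r tends to rise and the loss (1 - r)/2 shrinks.
- **The result would be biased.** Omitting baseline does not bias the randomized comparison on average. It costs precision and leaves a shift in the particular trial where arms start unequal.

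**Conclusion.** The point holds in conditional form. The covariate list stated for all models omits the baseline score of the outcome, while the analysis compares change from baseline and the score is already collected. Unless baseline is a response with a common mean across arms, which the text does not state, the loss relative to baseline adjustment is about (1 - r)/2. That is 30% to 15% for an assumed r of 0.4 to 0.7, 35% at 0.3 and 10% at 0.8, under equal variances, complete data and no credit for the four covariates. A reader might infer from Step 4 that the trial is underpowered. The article does not support that, because it does not say what the 36 per arm presumes. This is a precision issue with a cheap remedy and should be corrected; it does not threaten the validity of the randomized comparison.

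**What to change.** In Statistical Methods for Primary and Secondary Outcomes, state how baseline enters the model, in one of two ways:

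1. Post-intervention and follow-up scores are the responses. The model contains arm, visit, arm by visit, the baseline value of the outcome and baseline by visit.
2. All three assessments are responses, with the arm means constrained to be equal at baseline. This is equivalent for the present purpose and also keeps participants who have only a baseline value.

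Apply the same choice to GAD-7, PHQ-9 and each secondary outcome. Keep the four listed covariates and say that they are measured at baseline.

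The cost is a sentence or two and the matching model terms. No assessment, visit or participant is added.

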#### Statistical Methods for Additional Analyses

Secondary analyses will mainly explore the complex associations between all outcomes. To this end, correlation analyses will be carried out between symptomatic and other psychological variables. Multiple regression analyses and logistic regression analyses among all variables, particularly between mindfulness skills and anxiety symptoms, rumination and depression symptoms, and gender and symptomatology variables will be carried out. Lastly, group comparisons by gender and hours of app use will also be performed. The analysis will be carried out with SPSS 26.

#### Interim Analyses

There will not be interim analyses because the data will be analyzed at the end of the trial.

#### Methods in Analysis to Handle Protocol Nonadherence and Any Statistical Methods to Handle Missing Data

Primary outcomes will be assessed using an intention-to-treat analysis. Missing data will be reduced to a minimum by (1) rendering it impossible to advance on the app if a questionnaire is not completed in full, and (2) using the appropriate measures to encourage participants to fill out the follow-up questionnaires. Multiple imputations will be used to handle any missing data in the analyses.

### Oversight and Monitoring

#### Composition of the Coordinating Center and Trial Steering Committee

Daily support for the trial will be provided by the lead investigator, who supervises the trial. Additionally, the study coordinator helps with trial registration and will coordinate and oversee the study visits and reports while organizing data collection and assuring data quality. The data analyst will handle the database and carry out all primary and secondary analyses once all data are collected. Lastly, the app developer will design and implement all content of the app, ensuring the proper functioning of fundamental features such as the randomization of participants, completeness of data collected, automatic creation of the database, etc. The main study team will meet weekly during the duration of the study and monthly with a secondary group of expert collaborators. There is no trial steering committee, stakeholder, or public involvement group. The Ethical Scientific Committee of the Universidad de Talca will check the completeness of the investigation.

#### Composition of the Data Monitoring Committee, Its Role, and Reporting Structure

A monitor from the Ethical Scientific Committee of the Universidad de Talca will check once a year the presence and completeness of the investigation. This committee is independent of the sponsor and has no competing interests. For further details, please contact [contact].

#### Adverse Event Reporting and Harms

The intervention does not cause any harm to the participants. However, if participants experience emotional distress upon using the app, they can contact the lead investigator at any time, who can provide them with options for referral to other public mental health services available. This procedure is explained in detail in the informed consent and initial training videos.

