## Abstract

**Background:**

The prevalence of depression and anxiety has increased in recent years, with many individuals having trouble accessing mental health support. Smartphones have become an integral part of modern life, with apps offering new ways to deliver evidence-based self-help strategies to cope with common mental health symptoms. However, most of them do not have empirical evidence of their overall effectiveness or the effectiveness of their components, which could pose a risk for users.

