## Introduction

### Background and Rationale

Mental health disorders are common in the general population. In Chile, depression and anxiety are the most frequently observed psychopathologies, with a prevalence of 5% for depression and 6.5% for any form of anxiety [1]. However, the population affected by depression or anxiety symptoms may be greater, with 49.2% of Chileans reporting some level of depression symptoms [2]. These prevalences have become a significant issue in public health settings, where waitlists in public mental health services in Chile are mostly stagnant [3], and in the past 2 years have become extensive due to the COVID-19 pandemic. Thus, it becomes necessary to find alternatives that allow providers to respond to this need for mental health access [4].

In this context, the use of remote self-guided psychological interventions, such as those found in mental health mobile apps, has gained popularity [5]. It has been reported that this remote modality improves access, reduces waiting times for appointments, saves time, and reduces the effect of attitudinal barriers in patients seeking psychological support [6]. Studies indicate a high effectiveness rate of web-based care, with smartphone-based psychological interventions reducing user anxiety [7] and depression [8,9]. Accordingly, there has been an increased number of mental health mobile apps available to users. However, many of them do not have sufficient theoretical support for their effectiveness. In 2015, a total of 447 apps related to cognitive behavioral therapy (CBT) were found available in any App Store [10]. Conversely, 9 studies regarding the use of smartphones in cognitive-behavioral interventions were found, of which only 2 had readily available apps in the market [10]. Moreover, 10% of those who say they use cognitive behavioral interventions as a theoretical basis were not evidence-based [11]. It has been suggested that, without empirical support, these apps can be potentially harmful to users [12].

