Among the small portion of mobile apps that have empirical support for their tools, 3 specific components or modules have the highest rates of applicability and effectiveness for reducing depression and anxiety: assessment, education, and self-regulation digital tools [13]. The assessment component allows for the recognition of the current symptomatic state of the user, while the constant evaluation helps the monitoring and the development of awareness of the process of change in the symptomatology [14]. The psychoeducation process allows users to be informed about what they are experiencing. Although psychoeducation alone is an effective strategy for the improvement of some anxiety and depression symptoms [15,16], its effectiveness increases when it is accompanied by other strategies [17]. The final component, the use of self-regulation tools, demonstrates a series of brief, easy-to-use self-guided activities that attempt to regulate, express, or otherwise manage psychological distress, low mood, and symptoms of anxiety.

The presentation of these modules normally follows the theoretical framework of CBT. This treatment model can be easily adapted to non–face-to-face environments and has been repeatedly tested in web-based modalities [18,19]. Moreover, other approaches theoretically derived from CBT, such as behavioral activation therapy or mindfulness-based behavioral therapy, also exhibit evidence of their effectiveness in non–face-to-face settings [20]. The behavioral activation treatment for depression attempts to regulate depression symptoms through the programming of pleasurable activities [21], while mindfulness-based CBT focuses primarily on breathing techniques, relaxation, self-compassion, and mindfulness abilities [22], aimed at regulating anxiety states.

According to the literature, there are no mobile apps with scientific support to address depression and anxiety symptoms in the adult population in Chile. The regular and widespread use of such apps could help provide self-care tools to individuals who are reticent about therapy.

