### Eligibility Criteria

Adult Chilean citizens, 18 years of age or older, with access to a computer, tablet, or smartphone (Android or iOS) with internet, and no untreated mental health diagnosis, will be included in the study. The mental health diagnosis and current treatment will be assessed solely by the participant’s self-report.

Individuals who self-report substance abuse problems or any current serious mental health disorder and participants reporting scores greater than 1 on question 9 (suicidal ideation) on the Patient Health Questionnaire–9 (PHQ-9) will be excluded from the study.

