## Results

The trial is not yet recruiting and is expected to end in October 2024. The first results are expected in late April 2024.

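### The harms section states before recruitment that the app causes no harm, and the article describes no count that would show participants who get worse

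*Protocol article*

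**What the plan says.** The section Adverse Event Reporting and Harms opens with "The intervention does not cause any harm to the participants". It then allows that "if participants experience emotional distress upon using the app, they can contact the lead investigator at any time", and the lead investigator can offer referral options. The article describes no other provision for harms. It does not say that such contacts are recorded or reported by arm.

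Other parts of the article bear on that opening sentence:

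- Results: "The trial is not yet recruiting and is expected to end in October 2024".
- Abstract, Background: most mental health apps lack evidence of effectiveness, "which could pose a risk for users".
- Background and Rationale: "It has been suggested that, without empirical support, these apps can be potentially harmful to users", and the authors find that "there are no mobile apps with scientific support to address depression and anxiety symptoms in the adult population in Chile".
- Outcomes: GAD-7 and PHQ-9 are measured in all arms at baseline, post intervention and 1-month follow-up. PHQ-9 includes question 9, which is also used at entry: Eligibility Criteria excludes "participants reporting scores greater than 1 on question 9 (suicidal ideation").
- Statistical Methods: a mixed model for repeated measures compares change between arms. The additional analyses are correlations, regressions, and comparisons by gender and hours of app use.
- Criteria for Discontinuing or Modifying Allocated Interventions: data from participants who leave are not analysed.

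**The concern.** Whether the app harms anyone is something this trial could help to answer. The harms section treats the question as closed before any data exist. What the article then describes fits that premise: a referral route that depends on the participant making contact, and an efficacy model for means.

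Three consequences follow if the article is carried out as written. Self-initiated contact is likely to under-count distress. A comparison of means can favour a strategy arm while a minority in that arm deteriorates. And someone who worsens and leaves is removed from the data altogether. This matters because the Discussion foresees wide implementation in Chile and other Spanish-speaking countries if effects are positive.

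**Working it through.** **Is there support for the sentence in the article?** The trial has not started recruiting, and no earlier safety data for this app are cited. The components are described as evidence-based, but that evidence concerns effectiveness, and effectiveness of similar components elsewhere does not establish absence of harm here. The sentence is unconditional, while the one after it provides for distress on using the app. So the assertion has no stated basis and fits poorly with its own paragraph.

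**Sample size available.** From Sample Size: 36 per arm, 26% dropout, 4 arms.

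- 36 / (1 − 0.26) = 48.65, rounded up to 49 per arm; 4 × 49 = 196. The plan's figures reproduce.
- Three strategy arms pooled: 3 × 49 = 147 randomised, 3 × 36 = 108 completers.

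**What could zero events show?** With no events among n participants, the exact upper limit is 1 − 0.05^(1/n) for a one-sided 95% limit, and 1 − 0.025^(1/n) for the upper end of a two-sided 95% interval.

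| Group | n | One-sided 95% | Two-sided 95% |
|---|---|---|---|
| One arm, randomised | 49 | 5.9% | 7.3% |
| One arm, completers | 36 | 8.0% | 9.7% |
| Strategy arms, randomised | 147 | 2.0% | 2.5% |
| Strategy arms, completers | 108 | 2.7% | 3.4% |

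The control arm also uses the app (monitoring and psychoeducation), so all 196 are exposed to it. For n = 196 the one-sided limit is 1 − 0.05^(1/196) = 1.5%. No row reaches zero.

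**What would a by-arm count yield?** The article gives no deterioration rate, so the rates here are assumptions.

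- If the true rate in an arm were 5%, the chance of at least one case is 1 − 0.95^49 = 92%, or 1 − 0.95^36 = 84%. At 2% it is 63% or 52%.
- Two cases in 49 would be 4.1%, exact 95% interval 0.5% to 14.0%. Five in 49 would be 10.2%, interval 3.4% to 22.2%.
- Power for one strategy arm against control (two-sided 0.05, 36 to 49 per arm): 5% v 10%, 12–15%; 5% v 15%, 29–38%; 5% v 25%, 67–80%.

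A count would therefore probably pick up worsening if it occurs at a few per cent, but could not test a difference between arms unless that difference were large. It is descriptive.

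**Does the planned analysis fill the gap?** In part. The mixed model on PHQ-9 and GAD-7 would show average worsening in an arm. It would not show individual worsening offset by improvement in others, and none of the listed additional analyses counts participants who worsen. No interim analysis is planned, and the ethics committee's annual check, as described, concerns the presence and completeness of trial files.

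**Who would be in the count?** The discontinuation section removes leavers' data, while Statistical Methods and the section on nonadherence and missing data both promise intention to treat. With 26% dropout expected (13 of 49 per arm: 49 − 36), a table built under the discontinuation rule could lose the people most relevant to harm.

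**The case against.** The strongest reply is that this is one loosely worded sentence in a condensed article. A deterioration table would normally sit in the full protocol or analysis plan, which are not shown, and nothing in the harms section says that worsening will not be tabulated. That stands as far as it goes: absence of the table alone would not be a finding. It does not answer the assertion itself, which is printed in the harms section and which no unseen document would correct.

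Other parts of the reply also stand and limit the point:

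- The background warning concerns apps without empirical support, and the authors regard their components as evidence-based. A reader might infer that the article calls its own app harmful. It does not; it acknowledges a possible risk for a class of apps.
- A reader might infer that the eligibility rule on question 9 contradicts the harms section. It does not. One is an entry criterion and the other a referral procedure, and an entry threshold commits the protocol to nothing after randomisation.
- A reader might infer that the trial will report no harm without having looked. No section commits to that. Mean change is compared at both later time points, and Dissemination Plans promises complete disclosure of results.
- The zero-event limits would apply to any trial of this size. They show that the sentence cannot be supported, not that harm is likely.
- Every arm receives the app, so a by-arm table cannot show whether the app itself causes harm.

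**Conclusion.** The point holds as a wrongly stated premise in the harms section, together with a description of harm capture too thin to test it. The article gives no data for the claim, and this sample could not establish it: zero events would still leave one-sided 95% upper limits of 5.9% to 8.0% per arm and 2.0% to 2.7% in the pooled strategy arms. These limits assume independent participants and full ascertainment in the stated n. The power figures rest on assumed deterioration rates.

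It changes no primary test, estimand or sample size. It does not show that the app is harmful, that the eligibility and harms sections conflict, or that worsening will certainly go uncounted in documents not shown.

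**What to change.** 1. Replace the opening sentence of the harms section with a statement that harm is not known and will be assessed.
2. Pre-specify a descriptive table by arm, with 95% intervals, of participants whose PHQ-9 or GAD-7 score worsens from baseline by a margin the investigators fix in advance, at post intervention and at follow-up, with the number observed as well as the number randomised. Add the number with question 9 above the entry threshold after randomisation. How such scores are handled clinically is for the sponsor.
3. State that the table contrasts each added strategy with monitoring plus psychoeducation, not the app with no app, and that it is not powered for a test.
4. Retain data collected before a participant leaves, as far as consent allows, and reconcile the discontinuation section with the two intention-to-treat statements, so that those who worsen and leave are counted.

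Items 1 to 3 cost a few sentences and one table from scores already collected. Item 4 may require a change to the consent wording. Distress contacts could be tabulated too, but the article does not say that they are logged, so that would mean new recording.
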